### 5 MEASUREMENTS

#### 5.1 Dual energy x-ray absorptiometry (DXA)

Body composition and BMD will be assessed by dual x-ray absorptiometry (Lunar iDXA, GE Healthcare, Madison, USA) in an overnight-fasted and rested state. Participants are placed on the DXA scanner in their underwear, and the procedure will last maximally 20 minutes. Whole and regional lean body mass, fat mass, and body fat percentage, as well as total body, spine, bilateral hips, femoral necks, and distal femur BMD (absolute and t- and z-scores) are analysed by the enCORE software. Trained lab engineers and researchers will perform the DXA scans and analyses.

The DXA scanning includes imaging of the whole body for determination of fat mass and fat free mass (radiation dose ~0.003-0.008 mSv). In addition, images of the lumbar spine (radiation dose ~0.005 – 0.014 mSv) and hip (radiation dose ~0.002 – 0.004 mSv) will be made for the assessment of bone density. The cumulative effective dose will be ~0.010 – 0.026 mSv. In comparison, the daily radiation dose from natural sources in Norway (cosmos, air, food, soil) is ~0.011, and the radiation dose from a one-way intercontinental flight is ~0.050 mSv. Thus, the radiation involved in this study is marginally higher than the daily radiation dose from natural sources, but substantially lower than an intercontinental flight. However, for extra caution, female participants will be asked about (planned) pregnancy. If the time between screening and test day 1 exceeds 6 weeks, an additional scan will be performed at test day 1.

#### 5.2 Blood sample

One blood sample is taken in a fasted state at three visits. Biomarkers for nutritional status (i.e., s-iron, s-ferritin, b-triglycerides, s-vitamin B12, s-folate, s-vitamin D), health status (i.e., b-Hb, s-CRP, s-

TSH, s-T3/T4, s-FSH, s-LH, s-oestradiol/testosterone) and bone metabolism (i.e., s-albumin, p-PTH, s-calcium, s-CTx, bALP, s-P1NP) will be assessed. Analysis will be performed in accordance with SOP at Furst Laboratories. Blood samples will be taken by trained bioengineers and researchers.

### 5.3 24h dietary recalls

Dietary intake assessments will be conducted by three unannounced 24-hour dietary recalls for two weekdays and one weekend day, selected randomly within the 2-week test period around the test day. A single 24-h recall takes ~30-45 minutes to complete. The recalls are conducted by 1-2 trained nutritionists. Recalls will be assessed with the validated 5-step multiple-pass method to increase accuracy [10], and a checklist at the end [11]. This method consists of five steps: (a) the quick list, which is an uninterrupted listing by the subject of foods and beverages consumed; (b) the forgotten foods list, which queries the subject on categories of foods that have been documented as frequently forgotten; (c) a time and occasion at which foods were consumed; (d) the detail cycle, which elicits descriptions of foods and amounts eaten aided by the interactive use of the USDA Food Model Booklet and measuring guides; and finally (e) the final probe review. All recalls will be checked for completeness and will be processed with the Norwegian food database Kostberegningssystem (KBS) by one single nutritionist.

### 5.4 Muscular strength and rate of force development

Muscular strength and rate of force development (RFD) will be assessed in the key exercises of the intervention protocol (isometric overhead press, bench press, prone row, and supine horizontal pull). Each exercise will be tested with a load cell measuring the force applied upon it. Maximal and average force and rate of force development over the isometric contraction will be measured and analysed with Qualisys Track Manager (Qualisys AB, Sweden).

### 5.5 Physical function

Physical function will be assessed by the Transfer Assessment Instrument (TAI) 4.0, which is a step-by-step assessment of the quality of the way in which the wheelchair user transfers (Worobey et al., 2018), and by the time to transfer from wheelchair to chair/physio bench (see attachment G1).

### 5.6 Questionnaires

All questionnaires will be administered, collected, and processed digitally through NIH's secure area using TSD. TSD is an online platform which provides a safe project area with an integrated solution for collection, storage, and processing of sensitive data, and that meet the Norwegian data handling laws.

All questionnaires will be administered at baseline, at week 12 and week 24, except the Background questionnaire, which is only administered once, at the Screening. The participants will approximately use 60 minutes filling in all questionnaires at one time-point, except the background questionnaire which will take approximately 20 minutes. Both the intervention and control groups will fill in the questionnaires with a time construct of one week.

#### 5.6.1 Background, medical and physical activity screening questionnaire

Background and medical questions will be included at the screening to ensure eligibility of the participants to be included in the study. This includes both a pre-screening phone call (see attachment "*SOP Pre-screening telefonsamtale*"), digital questionnaire and physical screening visit. The background questions focus on the participants characteristics (sex, age, height, weight, diagnoses, use of medications, need/use of personal assistance, sports history, and other diseases [attachment Q1]). The questionnaire will also enable us to check whether the participants should be excluded based on [4.3 Exclusion criteria](#). The validated 7-item International Physical Activity

Questionnaire (IPAQ) short, adapted for persons with disabilities (Saebu, 2010), will be used to assess initial physical activity level and will be used to stratify the subsequent randomization of the participants to intervention and control groups. It will further be used to assess changes in PA over the study period (attachment Q2).

### 5.6.2 Functional health

To assess functional health, the participants will fill in the 16-item Spinal Cord Independence Measure (SCIM), which is a validated adaptation of the Functional Independence Measure (FIM) for SCI patients. It is our opinion it will transfer well to others wheelchair users. See attachment Q3.

### 5.6.3 Risk of low energy availability

To assess the risk of relative energy deficiency in sport (RED-S), the validated questionnaires Low Energy Availability in Females (LEAF) and Low Energy Availability in Males (LEAM) will be filled in by female and male participants, respectively (see attachment Q4A and Q4B). These questionnaires are validated in several languages, and the Norwegian versions will be used.

### 5.6.4 Mental health

Basic psychological needs satisfaction (autonomy, competence, and relatedness) will be measured as mediators (explanatory factors) to the mental health outcomes with the validated 12-item Basic Psychological Needs Satisfaction instrument for exercise (Chen et al., 2015). A variation of outcome measures is deliberately chosen to capture the multi-facet construct of mental health. Overall well-being is measured by the widely used and validated World Health Organization's 5-item Well-being Index (WHO-5 Wellbeing Index) (WHO, 1998). Exhaustion will be measured by a subscale from the Athlete Burnout Questionnaire (ABQ) (Raedeke & Smith, 2001). Five items are answered on a Likert scale with the following stem: "How often do you feel like this?" and the following anchors: (1) almost never, (2) rarely, (3) sometimes, (4) frequently, and (5) almost always.

Fatigue (8 items) and vigour (7 items) will be measured using two subscales from The Profile of Mood States (POMS) (McNair et al., 1971). The items (1-2 worded feelings the participant may have experienced in the previous week) are answered on a Likert scale with the following anchors: (0) not at all, (1) sometimes (2) moderately (3) fairly often, and (5) very often. See attachment Q5.

## 6 INTERVENTION

Based on the inclusion criteria screened participants will be invited to participate in the intervention. After attending the baseline testing, the participants are randomized into the intervention or control group. All testing is conducted at NIH, HVL or NTNU based on the participants living location.

[figure not shown]

**Figure 3: Schematic overview of the on-site visits during the study period.**

## 6.1 Baseline

All participants will arrive fasted for the baseline test day, which consists of a blood sample, breakfast, and the following testing: 1) muscular strength and RFD, 2) physical function, and 3) review of questionnaires (function, mental health, and risk of low energy availability). The test day takes a total of approx. 2.5 hours.

## 6.2 Nutrition

All participants will receive and be asked to consume a mixed powder supplement (FrieslandCampina, the Netherlands) that consists of vitamin D (800 IU), calcium (250 mg) and whey protein (30 g) per dose, on three days of the week throughout the 24-week study period, to ensure stable intakes of key nutrients for optimized bone remodelling conditions. The supplement can be mixed in water or milk as per preference.

In the two weeks around the baseline, on three different days (two weekdays and one weekend day), 24h dietary recalls will be carried out by a trained nutritionist by audio- or videocall with each participant. This will be repeated around the test days in week 12 and week 24. One dietary recall will take 30-45 minutes and is structured in several steps to ensure the participant recalls as much as possible.

## 6.3 Exercise intervention

The exercise intervention involves: 4 weeks of 3 sessions per week with supervised resistance training. Each session takes approximately 30 minutes. The training is carried out on-site (NIH, HVL or NTNU). From week 5, the participants train the 3 weekly sessions on their own in a suitable training site, with continued training at the study site one session every month throughout the rest of the intervention. During the entire period (24 weeks) the participants in the intervention group will complete 15 sessions at the study site and 57 sessions on their own.

The control group will not receive the exercise intervention and be asked to continue with their normal daily activities.

All participants will log their training and or physical activity, including the exercise intervention sessions for the intervention group (see attachment D3).

## 6.4 Mid- and post-intervention testing

In week 12 and week 24, all participants will attend new test days. On these test days the following testing will be conducted fasted: 1) DXA scan and 2) blood sample, before breakfast is provided and subsequent testing as follows: 3) muscle strength, 4) function (transfer from wheelchair to regular chair), and 5) review of questionnaires (function, mental health, and risk of low energy availability). These test days will also take approximately 2.5 hours.

## 6.5 Follow up

The intervention group will be contacted biweekly per telephone after the initial on-site training period for a short follow up conversation about how their exercise intervention is going.

All participants will receive feedback and counselling based on the dietary recalls and blood sample values after each test period. They will subsequently be administered commercially available supplements as per need if values are below Norwegian clinical reference values and or IOC guidelines for sport nutrition. Doses administered will be determined on individual basis by registered dietician and project lead [name] candidate and nutritionist [name] and or medical advisor [name].

Project partners medical advisor [name] (MD), physiotherapist [name] (PhD(c)) or Associate [name] (responsible for the mental health aspect of the study), will be sought to discuss any issues the participants may experience during the intervention and participants may be excluded from further participation and referred to their GP/the Norwegian Health care system for follow up in the case of discovery of serious medical issues.

After the study period, the participants will receive their last feedback and counselling session, as per, and within 6 months receive personal information about their bone health and physical progression in physical tests (muscular strength, rate of force development, function).

## 6.6 Focus interview

We will invite 10 willing participants from the intervention group (at random if more >10) to individual focus interviews after the end of the training period, where the participants' experiences from the exercise intervention will be discussed. This is voluntary and does not otherwise limit participation in the study. The conversation will be audio recorded with the consent of the participants, and the participants will be anonymized. An interview guide will be followed (attachment G1).

## 6.5 Estimation of time use

Estimated time spent on testing, intervention, and training:

- Screening: approx. 2.5 hours attendance in the lab
- Testing: A total of 3 days with approx. 2.5 hours attendance in the lab (at start-up, week 12 and week 24).
- Resistance training supervised at one of the test sites (training group only): 30 minutes 3 days a week for 4 weeks + 3 extra days (months 2, 4 and 5) during the intervention period.
- Resistance training (training group only): 60 minutes 3 days a week for 20 weeks - 3 extra days supervised at the test site (see point above).
- Focus interview (10 participants of the intervention): Approx. 1-hour physical conversation or videocall after the final test day has been completed.

# 7 STATISTICAL ANALYSIS

## 7.1 Statistical Analysis

Cross-sectional data from screening will be analysed by itself, except participants characteristics and DXA results (pre-intervention) which will also be utilized in the analyses of the RCT data. The cross-sectional data will be analysed descriptively. However, depending on the study population, subgroup comparison analysis can be performed (e.g., athlete vs non athlete; males vs females; hypertonia vs non-hypertonia; spinal cord injuries vs cerebral palsy vs amputees). To analyse the group effects over the intervention period, linear mixed model for repeated measures with an unstructured covariance structure will be used. Random intercept and slope for subjects and fixed effects of time, treatment and their interaction will be included in the model. The interaction term accommodates different patterns of change over time between intervention and control group. The mixed model allows all outcome data to be used, regardless of whether an individual has complete data or not, making these models consistent with an intention-to-treat analysis. Correlation tests between delta change of main parameters and background variables will also be performed. Data will be analysed both per protocol and by intention-to-treat.

A p-value < 0.05 will be considered statistically significant. Data will be analysed by IBM SPSS statistics.

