## 4 PARTICIPANTS

### 4.1 Number of participants

Power calculation is performed using GPower 3.1. The primary outcome and focus of the RCT is change in BMD of the spine. Mean and standard deviations for a relevant difference between intervention and control group is based on a previous 24-week exercise intervention that showed a significant increase in BMD of the spine of 3.5 % (Rubin et al., 2020). Based on an 80 % power at a significance of  $P=0.05$ , the sample size needed to detect a relevant change in BMD of the spine would be 22 persons in each group. To account for a potential 35 % dropout rate, **30 participants** will be included in each group. Based on ~39% prevalence of BMD Z-score of the spine  $\leq 0$  SD in the wheelchair users in the ParaNut study (unpublished), we assume ~150 participants need to be screened. However, in order to reach this number of participants, we include wheelchair users with BMD Z-score  $<0$  at any measured site. We believe that a participant with Z-score  $>0$  at lumbar spine also could benefit from the intervention. Furthermore, as Z-scores of the hip and femur neck are secondary outcome parameters, we choose to include participants with a Z-score  $<0$  at any measured site.

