#### 4.5 Randomization

Based on physical activity level, each participant will be categorized as non-active, moderately active, and very active (see 5.6 Questionnaires). Eligible participants will be randomly assigned to one of the two study groups, an intervention group (n=30) or a control group (n=30). The randomization list will be created using Randomizer.org, and stratified by physical activity status, sex, and SCI/non-SCI, with a 1:1 allocation using random block sizes of 4, 6, and 8. To ensure allocation concealment, we will use sequentially numbered, non-transparent envelopes containing the treatment allocation information. The groups will be checked for distribution of age, medication use, degree of injury/disability, and degree of wheelchair use.

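### The model in section 7.1 names none of the factors used to stratify randomization; if those factors predict change in BMD, its intervals are somewhat too wide and its test mildly conservative

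*Protocol*

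**What the plan says.** Section 4.5 describes randomization "stratified by physical activity status, sex, and SCI/non-SCI, with a 1:1 allocation using random block sizes of 4, 6, and 8". Activity has three levels: "each participant will be categorized as non-active, moderately active, and very active". That makes 3 × 2 × 2 = 12 strata for 60 people. Site is not a stratification factor, although section 6 states that "All testing is conducted at NIH, HVL or NTNU based on the participants living location".

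Section 4.1 states that "The primary outcome and focus of the RCT is change in BMD of the spine", so the contrast of interest is treatment by time. For the analysis, section 7.1 says that a "linear mixed model for repeated measures with an unstructured covariance structure will be used". It adds "Random intercept and slope for subjects" and "fixed effects of time, treatment and their interaction will be included in the model". It names no stratification factor, site or baseline covariate among the model terms.

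**The concern.** The analysis does not follow the design. When allocation is balanced within strata, the part of the outcome that the strata explain largely cancels between arms, so the true sampling error of the treatment effect falls. A model without the strata leaves that part in the residual. Its standard error is then too large, its intervals too wide and its test conservative.

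What is at stake is precision in a trial of 30 per group that plans for 35% dropout. The validity of the result is not at stake.

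**Working it through.** **The plan's own figure.** The 22 per group cannot be reproduced, because section 4.1 gives a 3.5% increase but no SD. With a two-sided 5% t-test and 80% power, 22 per group implies d = 0.865, that is an SD of change of 3.5/0.865 ≈ 4.0%. This d is used below. Completers at 35% dropout: 60 × 0.65 = 39, or 19.5 per group.

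**Upper bound under perfect balance.** Model SE over true SE is 1/√(1−R2): 1.054 at R2 = 0.1 and 1.118 at 0.2. The size of the unadjusted test is 2·(1−Φ(1.96/√(1−R2))): 3.9% and 2.8%. This overstates the effect here. Sixty people over 12 strata is about 5 per stratum, against blocks of 4, 6 and 8, so many blocks stay incomplete.

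**Simulation of the actual scheme** (12 strata, blocks of 4/6/8, unadjusted analysis of change). The first set used 8,000 runs per scenario:

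| R2 | SE ratio, N=60 | Type I, N=60 | SE ratio, N=44 | Type I, N=44 |
|---|---|---|---|---|
| 0 | 1.01 | 4.7% | 0.98 | 5.3% |
| 0.1 | 1.04 | 4.3% | 1.01 | 4.4% |
| 0.2 | 1.09 | 3.2% | 1.06 | 3.7% |

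Adjusted for the strata, type I error stayed between 4.6% and 5.3%. A second set gave, for R2 = 0.1 and 0.2, about 4.4% and 3.5% at N = 60 and about 4.7% and 3.7% with 39 completers. The simulation error of one such figure is √(0.04 × 0.96/8000) ≈ 0.2 points, so differences of a few tenths are noise.

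**Power.** The closed form (noncentral t, d = 0.865, 19.5 per group, charging only 4 df for the strata) gives 74.8% unadjusted. Adjusted, it gives 74.6%, 78.9% and 83.4% at R2 = 0, 0.1 and 0.2. This flatters adjustment in two ways. Stratification has already lowered the true error of the unadjusted estimate, and chance imbalance of covariates among 39 completers costs precision beyond the degrees of freedom. Simulation at 39 completers, which includes both effects, gives a gain of about 1 to 5 points at R2 = 0.1–0.2 and a loss of up to about 4 points at R2 = 0.

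**Which terms matter.** One simulated data set (60 people, three visits, complete data, unstructured covariance) was fitted three ways:

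- No strata: treatment by week 24 estimate 0.2630, SE 0.1296.
- Strata as main effects: 0.2630, SE 0.1296, unchanged. Only the SE of the treatment main effect moves (0.331 to 0.249), and that is not the effect of interest.
- Strata with time interactions: SE 0.1217.

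Stable differences in BMD level between strata already cancel from the treatment by time contrast; only differences in change matter. The fall to 0.1217 shows which terms can move the contrast. It comes from one data set and is no estimate of the gain.

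**Baseline as covariate.** The variance ratio to a change-score analysis is (1+r)/2, where r is the assumed correlation of baseline with follow-up: 0.75 at r = 0.5, 0.90 at 0.8 and 0.975 at 0.95. That is a 10–25% reduction for markers, strength and questionnaires if r is 0.5–0.8, and under 3% for BMD if r is 0.95 or more.

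**Degrees of freedom.** Baseline 1, baseline by visit 1, activity 2, sex 1, SCI 1: 6 in all. Site adds 2, making 8.

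**The case against.** Section 7.1 lists terms that will be included and does not say that there are no others. It also says that pre-intervention characteristics and DXA results will be used in the RCT analyses, and a separate SAP may hold a covariate list. This is fair as far as it goes. However, the protocol commits to a model by fixed effects, random effects and covariance structure, and a reader who follows it would fit it without the strata.

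The stronger objection is that nothing in the protocol shows that activity, sex or SCI status predicts change in BMD over 24 weeks. At R2 = 0 the unadjusted test is correct and adjustment only costs. This stands, and it makes the point conditional. With 39 to 60 people, a lean model is a defensible choice.

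A reader might infer more than the documents support:

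- That the intervals are certainly too wide, or that adjustment is free. Both depend on R2, which is not given.
- That the test size falls to 2.8–3.9%. This needs complete balance in every stratum, which 12 strata and these block sizes do not deliver.
- That leaving out site has the same effect. Site was not stratified, so allocation removed no site variation from the true error and the mechanism does not apply.
- That the treatment effect is biased or false positives are inflated. Neither follows; the error is towards caution.

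**Conclusion.** The point holds in a conditional and modest form. The named model omits the three factors that governed allocation. If they explain 10–20% of the variance in BMD change, the unadjusted test runs at about 4.4–4.7% to 3.5–3.7% instead of 5%, and adjustment would recover about 1 to 5 points of power at 39 completers. If they explain none, nothing is wrong with the intervals and adjustment costs up to about 4 points.

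This rests on an assumed R2 of 0 to 20%, a two-sided test, d = 0.865 as implied by 22 per group, and dropout at the planned 35%. It is a precision improvement worth deciding in advance and does not threaten validity.

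**What to change.** In section 7.1, model the week 12 and week 24 values with fixed effects for treatment, visit, treatment by visit, baseline value, baseline by visit, activity category, sex and SCI/non-SCI. If baseline stays in the outcome vector, use a constrained baseline (no treatment difference at baseline) with factor by visit terms, because main effects of the strata alone leave the treatment by time contrast unchanged.

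Site may be added as a separate precision covariate, justified by testing at three sites and not by the stratification.

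The change is one of wording, and all the variables are already collected. It costs about 6 model degrees of freedom, or 8 with site, plus the possible power loss given above; site would add to that loss if it explains nothing. If the sponsor prefers the leaner model, section 7.1 should say so and give the reason. Either choice should be fixed before outcome data are examined, so that covariates are not selected after the fact.
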